## Study status

At the time of submission of this protocol for publication, preventive agents have been identified from the literature and we have identified the corresponding molecular trait for each agent. We have determined which molecular traits are instrumentable and, for those that are (
Table 2), we have begun to identify genetic instruments.

**Table 2. T2:** Preventive agents identified in the literature to be associated with CRC risk reduction.

Preventive agent	Molecular trait
Dietary long-chain omega-3 polyunsaturated fatty acids	Circulating long-chain omega-3 polyunsaturated fatty acids
Dietary long-chain omega-6 polyunsaturated fatty acids	Circulating long-chain omega-6 polyunsaturated fatty acids
Dietary salicylic acid	Plasma salicylic acid levels
Dietary calcium	Serum calcium levels
Dietary vitamin D	Serum 25 hydroxyvitamin D
Dietary folate levels	Serum folate levels
Dietary selenium	Circulating selenium levels
Dietary vitamin A	Serum retinol levels
Dietary vitamin C	Plasma vitamin C levels
Dietary vitamin E	Circulating alpha-tocopherol levels
Dietary β carotene	Circulating β carotene levels
Dietary magnesium	Serum magnesium levels
Statins	Circulating LDL cholesterol levels (due to HMG-CoA reductase inhibition)
Guselkumab	Plasma IL23 protein levels
Antihypertensives	Serum ACE levels
	SBP (due to NCC inhibition)
	SBP (due to ADRB1 inhibition)
Testosterone	Circulating testosterone levels
Estradiol	Serum estradiol levels
Sex hormone binding globulin	Serum SHBG levels
Progesterone/17- hydroxyprogesterone	Circulating progesterone/17- hydroxyprogesterone levels

Abbreviations: CRC = colorectal cancer; LDL = low-density lipoprotein; HMG-CoA = 3-hydroxy-3-methylglutaryl coenzyme A; IL23 = interleukin 23; ACE = angiotensin-converting enzyme; SBP = systolic blood pressure; NCC = sodium chloride cotransporter; ADRB1 = β1 adrenoceptor; SHBG = sex hormone binding globulin. Preventive agents identified in the literature that had a corresponding molecular trait that was deemed instrumentable. These agents included dietary micronutrients, drugs and endogenous hormones. For each drug, the biological target of the drug was identified as it’s molecular trait, (e.g. the levels of the protein that the drug targets). For dietary micronutrients and endogenous hormones, molecular traits were identified that correspond to the agent (e.g. blood-based biomarkers for vitamin levels).

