## Methods

### Study design

Two-sample MR will be used to investigate the causal relationship between putative preventive therapy agents and risk of CRC. The preventive agents investigated in these analyses will include medications, dietary micronutrients and endogenous hormones. We are prioritising these types of agents as they can be modified through either supplementation (e.g. increasing vitamin levels) or pharmacological perturbation (e.g. inhibiting protein drug targets). For previously reported medications, we will attempt to instrument the target of these medications (e.g. circulating protein targets). For previously reported dietary micronutrients, we will instrument circulating measures of these micronutrients (e.g. blood-based biomarkers for dietary vitamins). For circulating endogenous hormones, these will be instrumented directly. For simplicity we will collectively refer to the different instrument classes (e.g. circulating targets of medications, circulating dietary biomarkers, and circulating endogenous hormones) as molecular traits. Genetic instruments for each molecular trait will be constructed using single nucleotide polymorphisms (SNPs) associated with these molecular traits, obtained from summary statistics of genome-wide association studies (GWASs). We will then extract these SNPs from an independent GWAS of CRC risk to estimate causal effects. The Strengthening the Reporting of Observational Studies in Epidemiology using Mendelian Randomization (STROBE-MR) guidelines (up to and including the methods section)
^
24
^ were used to structure the writing of this protocol.

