For those molecular traits that will be taken forward for further analyses, genetic instruments will be constructed by identifying GWASs that have reported genetic associations with direct measures of molecular traits of interest in populations of European ancestry. These studies, and available instruments, will be searched for using several databases. Firstly, the GWAS catalogue
^
27
^ and the IEU Open GWAS
^
28
^ will be searched, followed by PubMed and medRxiv/bioRxiv for any pre-prints. We will also consult in-house summary genetic association statistics, if necessary, to access restricted and unpublished datasets. Genetic instruments will be constructed by selecting SNPs strongly associated with each trait of interest (p<5°10
^-8^) using summary genetic association data from these studies. For those molecular traits that are protein drug targets or biomarkers, SNPs will be selected that are located in or within proximity to genes that code for that protein (termed
*cis*-variants).
*Cis*-variants are expected to be specific to the target being instrumented which should minimise the likelihood of bias from horizontal pleiotropy. In addition, the use of
*cis*-acting variants that influence protein targets of drugs examined would be expected to enhance instrument strength because protein expression is relatively proximal to germline genetic variants. In the absence of SNPs associated with direct measures of protein targets, we will explore constructing instruments from SNPs associated with downstream biomarker perturbations of drug targets. For those molecular traits that correspond to dietary agents or endogenous hormones, genome-wide significant variants will be selected independent of their genomic position. Of these variants, only those that are independent (r
^2^<0.001) will be included as instrumental variables in the primary analyses. For protein drug targets and biomarkers, we will increase the number of SNPs in our genetic instrument by permitting SNPs to be in weak linkage disequilibrium (e.g. r
^2^<0.10). We will account for this by generating a correlation matrix using a random subset of 10,000 individuals of white British ancestry in the UK Biobank as reference panel and using a generalised IVW method that can account for correlated instruments
^
29
^.

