### Main analyses

The proportion of variance in the molecular traits explained by the SNPs used as instrumental variables (r
^2^) and the strength of the instrument (F-statistic) will be calculated. The F-statistic can be used to test the “relevance” assumption and a threshold of >10 indicates that weak instrument bias is unlikely
^
35
^.

The proportion of variance explained in the instruments (R2) will be calculated using the following formula: 

$$R^{2}=\frac{2\beta^{2}MAF(1-MAF)}{2\beta^{2}MAF(1-MAF)+{\left(se(\beta )\right)}^{2}(2N)MAF(1-MAF)}$$

Where β is the effect size (beta coefficient) for a given SNP, MAF is the minor allele frequency, se(β) is the standard error of the effect size, and N is the sample size. 

F-statistics will be calculated using the following formula:

$$F=R^{2}(N-2)/(1-R^{2})$$

Where R2 is the proportion of variance explained in the instrument, N is the sample size

For molecular traits instrumented by a single SNP, the Wald ratio will be used to calculate the effect of the molecular exposure on CRC risk
^
23
^. For those traits that are instrumented by more than one SNP, the inverse-variance weighted (IVW) method will be used
^
23
^. The multiplicative random effects IVW will be prioritised, except where the number of SNPs is limited (e.g. ≤3) in which case the fixed effects IVW will be used.

To account for multiple testing, we will use a false discovery rate (FDR) correction of <5% to define strong evidence.

We will attempt to explore analyses stratifying by cancer subsite (e.g. distal, proximal, colon, and rectal). This will require requesting access for restricted GWAS data
^
36
^.

We will explore conducting multi-variable MR (MVMR)
^
37
^ for significant findings (reaching an FDR corrected threshold of <5%) for which there is genetic overlap between instruments. We will use MVMR when we suspect this genetic overlap is more likely to reflect horizontal, as opposed to vertical, pleiotropy.

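### Genome-wide SNP selection for testosterone and estradiol, with the hormone fraction unstated, can let SHBG-acting variants into the hormone instruments, and no planned step targets this when the hormone result is null

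*Protocol article*

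**What the plan says.** Table 2 (Study status) names the exposures as "Circulating testosterone levels", "Serum estradiol levels" and "Serum SHBG levels", each in its own row. The words total, free and bioavailable appear nowhere in the article.

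Study design states: "For circulating endogenous hormones, these will be instrumented directly". Exposure data and instrument selection adds: "For those molecular traits that correspond to dietary agents or endogenous hormones, genome-wide significant variants will be selected independent of their genomic position". The selected SNPs are then pruned, and only those independent at r² < 0.001 "will be included as instrumental variables in the primary analyses". That pruning works within one trait's instrument. It does not compare the testosterone or estradiol instrument with the SHBG instrument.

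Main analyses foresees shared variants between exposures. MVMR will be explored "for significant findings (reaching an FDR corrected threshold of <5%) for which there is genetic overlap between instruments", with a further condition: "We will use MVMR when we suspect this genetic overlap is more likely to reflect horizontal, as opposed to vertical, pleiotropy".

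Sensitivity analyses provides leave-one-out for every multi-SNP instrument. With about 10 or more SNPs it adds weighted median, weighted mode and MR-Egger, supported by MR-PRESSO. Of the analyses in that section, only Steiger filtering is conditional on an FDR-significant result.

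**The concern.** SHBG, as its name says, carries sex hormones in blood. A variant that raises the carrier can raise the bound hormone, and hence a total-hormone measurement, without a matching rise in the unbound part. Under a position-free rule, a variant of this kind that reaches p < 5×10⁻⁸ for the measured hormone qualifies as a hormone instrument.

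The testosterone or estradiol estimate is then a mixture of the hormone's effect and whatever SHBG does. Two errors become possible:

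- an SHBG effect is reported under a hormone's name;
- a real hormone effect is diluted, or cancelled by an opposite SHBG effect, and reported as null.

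All three traits are on the study's own list of candidate agents, so telling them apart is part of the stated task. The same section prefers cis-variants for protein targets because they limit horizontal pleiotropy. The hormone rows do not have that protection.

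**Working it through.** **Plan's own figures.** The article gives no figure for overlap between the hormone and SHBG instruments, so there is none to reproduce. Figure 1 (power) is not visible. Its sample size adds up: 78,473 + 107,143 = 185,616.

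**Inputs from the document.** N = 185,616; case fraction K = 78,473/185,616 = 0.4228; odds ratios per SD of 0.8 and 0.9; R² of 0.005, 0.01 and 0.05; 5% significance level.

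**Assumed inputs.** s is the share of IVW weight from SHBG-acting SNPs, set at 0.25, 0.5 and 0.75. b is the log odds ratio per SD through the hormone. g is the log odds ratio of the SHBG-acting SNPs, per SD of measured hormone.

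**Formulae.** The IVW estimate is a weighted mean of SNP-specific ratios, so its expectation is (1 − s)·b + s·g. Power is Φ(√(N·R²·K(1 − K))·|log OR| − 1.96) plus the opposite tail. At R² = 0.01 the multiplier is √(185,616 × 0.01 × 0.4228 × 0.5772) ≈ 21.28.

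**False null** (g = 0, true OR 0.80, ln 0.80 = −0.2231). The expected OR is 0.80^(1 − s):

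| s | Expected OR | Power, R² = 0.005 | Power, R² = 0.01 | Power, R² = 0.05 |
|---|---|---|---|---|
| 0 | 0.800 | 0.919 | 0.997 | 1.000 |
| 0.25 | 0.846 | 0.712 | 0.945 | 1.000 |
| 0.50 | 0.894 | 0.390 | 0.661 | 1.000 |
| 0.75 | 0.946 | 0.134 | 0.221 | 0.756 |

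Worked case at s = 0.5, R² = 0.01: 21.28 × 0.1116 = 2.375; 2.375 − 1.96 = 0.415; Φ(0.415) = 0.661.

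For a true OR of 0.90 at R² = 0.01, power falls from 0.611 to 0.391, 0.202 and 0.087.

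**False hit** (b = 0, SHBG-path OR 0.80 per SD of measured hormone, R² = 0.01). The expected OR is 0.80^s:

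| s | Expected OR | Rejection at 5% | Rejection at 0.05/21 |
|---|---|---|---|
| 0 | 1.000 | 0.050 | 0.002 |
| 0.25 | 0.946 | 0.221 | 0.032 |
| 0.50 | 0.894 | 0.661 | 0.254 |
| 0.75 | 0.846 | 0.945 | 0.700 |

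The last column is the strictest step of an FDR procedure over the 21 molecular-trait rows of Table 2. The scale of g matters. Suppose the OR of 0.80 were per SD of SHBG, and SHBG SNPs raised the hormone by 0.5 SD per SD of SHBG (a further assumption). The expected OR would then be exp(s·ln 0.80/0.5), which is 0.894 at s = 0.25 and 0.800 at s = 0.5.

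**Limit of these figures.** They ignore the extra heterogeneity that a mixed instrument creates. Multiplicative random-effects IVW would widen the standard error for it.

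**What the planned checks reach.**

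- Leave-one-out can expose one dominant SHBG variant, but not several acting together.
- Weighted median, weighted mode and MR-Egger are planned only with about 10 or more SNPs. The median needs most of the weight to be valid. MR-Egger needs pleiotropic effects unrelated to SNP–exposure strength, and here both would run through SHBG.
- MR-PRESSO, by the article's own account, assumes that most SNPs are valid.
- Steiger filtering compares the hormone with CRC, not with SHBG.
- Colocalisation at an SHBG locus could support the hormone row even if SHBG were the cause, because the variant would be shared.
- MVMR is the only planned method that would separate the two traits. It requires a significant finding and a judgement that the overlap is horizontal. A path from SNP to SHBG to measured hormone could be read as vertical.

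**The case against.** The strongest reply is that the article does not commit to total hormone. A reader might infer that it does, but Table 2 says only circulating and serum, instrument identification has only begun, and the list of exposure studies is still being curated. This stands: the fraction is unspecified, and the problem is conditional on a total-hormone GWAS being chosen. The selection rule itself is stated, however, and nothing in it prevents that choice.

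A reader might also infer that MVMR is the sole protection. It is not. Leave-one-out, the three robust estimators and MR-PRESSO are not tied to FDR significance, so they would also run on a null hormone result. With a minority share such as 0.25, the weighted median is in the setting it was designed for. The r² < 0.001 rule also leaves few SNPs at any one locus, so leave-one-out could show up a single SHBG-region variant. This is real but partial cover, and it weakens as SHBG-acting SNPs become several, carry most of the weight, or sit in a small instrument.

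The false-hit side is partly anticipated by the MVMR plan. The false-null side is not, and it is the stronger half of the point.

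Finally, the document does not show that SHBG variants reach genome-wide significance for these hormones, or with what weight. This also stands: the mechanism is plausible from SHBG's role as a carrier, but the size is an assumption.

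**Conclusion.** The point holds as a gap in a stated rule. Position-free selection, an unstated hormone fraction and the absence of any SHBG screen allow the testosterone and estradiol rows to partly re-test SHBG. The planned checks cover this incompletely, and MVMR would not be run on a diluted or cancelled hormone effect.

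For an assumed share of 0.25 to 0.75, a true OR of 0.80 would be estimated as about 0.85 to 0.95. At R² = 0.01, power would fall from 0.997 to between 0.945 and 0.221. At the low end of the share the loss is small; at the high end the effect would usually be missed.

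The figures depend wholly on the assumed share, on SHBG-acting SNPs qualifying for the hormone instruments, and on total hormone being the measured trait. The documents do not support saying that the hormone rows are in fact contaminated, or by how much. Nor do they show that the primary exposure must become free or bioavailable hormone; that would change the exposure and is open to debate. This is a cheap improvement rather than an error that invalidates the plan.

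**What to change.** 1. State in Table 2 or in the instrument-selection section which fraction of testosterone and estradiol each exposure GWAS measures.
2. Prespecify MVMR of testosterone with SHBG, and of estradiol with SHBG, whatever the univariable FDR result, and report each beside the univariable estimate.
3. As a sensitivity analysis, repeat the testosterone and estradiol analyses without SNPs in the SHBG region and without SNPs more strongly associated with SHBG than with the hormone.

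The cost is one extra model per hormone and a SNP filter. SHBG is already a planned exposure, so its GWAS data are needed anyway. The filtered analysis will have a lower R² and wider intervals, and MVMR may be imprecise if few hormone SNPs are distinct from SHBG. Instrument identification is still under way, so the change can be made before results are known.

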## Dissemination

The findings from this study, along with any changes in methodology, will be submitted for open access publication in a peer-reviewed journal upon completion of the study.

## Ethics and consent

The CRC GWAS used in this study complies with all relevant ethical regulations and has been approved by the South Central Ethics Committee (UK) (reference number 17/SC/0079). As the list of studies to be used to instrument the molecular traits is still being curated, details on the ethical compliance of these studies will be provided with the results of the analyses described here.

## Data Availability

No data are associated with this article.
